### **Scope of the Project**

#### **Principal Objective**

- Evaluate cost-benefit deriving from the presumed reduced number of unnecessary excisions given the accuracy of diagnosis with RCM.
- develop and test a regional triage system for skin cancers based on a radial hospital network model with the systematic integration of RCM into current clinical practice.
- Evaluate diagnostic sensitivity and specificity in screening patients at high risk of skin cancer with the use of the manual RCM tool.

Experimental design 1 aims at a reduction of over 30% of unnecessary excisions, with less than 2% of melanoma delayed

diagnosis (compared with dermoscopy delayed melanoma diagnosis ranging from 7.6 to 16.2%, for digital monitoring (10)),

and with no tumors thicker than 0.5 mm delayed.

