#### **Secondary Objectives**

- Evaluate diagnostic accuracy of lentigo maligna with different clinical-instrumental algorithms.
- Define which RCM features distinguish lentigo maligna from benign facial macules, such as solar lentigo, freckles, actinic keratoses and seborrheic keratoses, and to develop an easy-to-use diagnostic algorithm.
- Evaluate the accuracy of basal cell carcinoma diagnosis with RCM.
- Analyze and compare the difference of costs of diagnosis with RCM compared to standard histological examination.
- Compare the time required to perform RCM compared to standard histological examination.

Hypothesis to be tested: the advantage of the integration of RCM to the current clinical-diagnostic pathway (clinical-dermoscopic). Outcomes will be measured in terms of the early diagnosis (number of unnecessary excisions), diagnostic safety (number of melanomas diagnosed), and cost-benefit / efficacy calculation based on the drug model. economic developed within the studio.

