### **Design and description of the study**

This is a prospective randomized 2-arm study (performed in 3 hospitals). Consecutive patients with at least 1 lesion suspicious of melanoma (following clinical and dermoscopy evaluation) will be enrolled. Patients will be randomized to the standard therapeutical care ("Clinical and dermoscopy evaluation only") or standard therapeutical care + RCM integration ("RCM evaluation + clinical and dermoscopy evaluation") following identification of a suspicious lesion during the standard therapeutical care.

The main objective is to evaluate the safety of the integration of RCM (diagnostic identification of melanomas) and cost-effectiveness in terms of the comparison of the number of excisions needed to identify 1 melanoma (including the follow-up period). A cost-utility model will be developed to quantify the impact of the proposed triage system on health care costs and diagnostic effectiveness. This model will be tested on the study population.

Patients will be selected consecutively among patients with suspected skin cancer.

Randomization will be allocated at a 1:1 ratio and patients will be allocated to the “RCM evaluation + clinical and dermoscopy evaluation” or “Clinical and dermoscopic evaluation only” following standard therapeutic care; patients allocated to “Clinical and dermoscopic evaluation only” will likely require immediate biopsy for diagnosis, whereas clinicians of patients allocated to the “RCM evaluation + clinical and dermoscopy evaluation” can decide based on RCM evaluation whether to excise the lesion or refer the patient to subsequent digital follow up. Lesions referred to follow-up will be monitored for at least 6 months, and excised if significant changes are observed on dermoscopy.

In detail, the therapeutic-diagnostic pathway for each study arm are as follows:

a) "RCM evaluation + clinical and dermoscopy evaluation": following routine therapeutic care (clinical-dermoscopic examinations) clinicians of patients with suspicious lesions (at least one major or minor clinical and / or dermoscopic criterion for malignancy, as per inclusion / exclusion criteria) will be able to evaluate the lesions with RCM. A clinical decision (removal or digital dermoscopic follow-up) will be made based on the RCM evaluation.

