### **Statistical analysis**

Randomization: the "sample" function of STATA 13 (STATA Corp. College Station, Texas 2014) will be used weekly to predetermine the allocation of the subjects, in an alternating random manner, into the two study arms.

In the Coordinating Center, an estimated 800 patients will be enrolled (a total of 400 cases per study arm).

Outcomes include diagnostic safety of the RCM tool (measured by the number of excisions in relation to the number of melanomas diagnosed), a cost-benefit / efficacy calculation (based on an economic-drug model developed within the studio).

The estimated number of delayed cancer diagnosis within the "RCM evaluation + clinical and dermoscopy evaluation" study group is less than 1%.

Study power calculation: The expected percentage of melanomas identified in the "Clinical and dermoscopic evaluation only" group is 7.3% (Carli P, De Giorgi V, Nardini P, Seidenari S, Pellacani G, Peris K, Piccolo D, Rubegni P, Perotti R. *Skin Cancer Day in Italy: tumor detection rate and pattern of referral of open access clinics in an intermediate melanoma risk population. Eur J Dermatol* 2003; 13: 76-79) and for the "RCM evaluation + clinical and dermoscopy evaluation" group is 14% (Guitera P, Pellacani G, Longo C, Seidenari S,

As outlined in literature, approximately 22.4% of patients with "atypical" lesions are sent for treatment in highly experienced centers, equipped with digital dermoscopy (Alarcon I, Carrera C, Palou J, Alos L, Malveyh J, Puig S. *Impact of in vivo reflectance confocal microscopy on the number needed to treat melanoma in doubtful lesions. Br J Dermatol.* 2014; 170: 802-8) therefore, the enrolment of at least 2375 patients is required. Each collaborating center will enroll about 800 subjects.

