The differences in the frequency of diagnoses obtained in the two study groups will be calculated and compared using the X2 test (chi-square). As a measure of diagnostic efficiency, the NNE (Number Needed to Excise), corresponding to the ratio between malignant lesions and excised benign lesions, obtained in the two different arms, will be calculated. Kolmogorov-Smirnov two-sample Z-test will be used to compare the differences in NNE obtained in the 2 arms. The cost - utility model will be developed in collaboration with the University of Pavia, Department of Pharmacological Sciences, in order to quantify the economic impact on the National Health System.

The model will take into account the costs of treatment (surgery / drug), examination, follow-up visits, devices and histopathology evaluation. The model will be constructed considering two possible alternatives: surgical excision versus RCM examination of equivocal lesions. The model will be tested and adapted based on the real data obtained from the prospective study.

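### Diagnostic safety is measured by excisions per melanoma, an efficiency ratio that looks no worse than control as long as the share of melanomas missed does not exceed the share of benign lesions spared

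*Protocol*

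**What the plan says.** The protocol attaches the word safety, and the ratio of excisions to melanomas, to different things in different sections.

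- Statistical analysis, list of outcomes: "diagnostic safety of the RCM tool (measured by the number of excisions in relation to the number of melanomas diagnosed". Here safety is the ratio.
- Statistical analysis, description of tests: "As a measure of diagnostic efficiency, the NNE (Number Needed to Excise), corresponding to the ratio between malignant lesions and excised benign lesions". Here essentially the same quantity is efficiency.
- Secondary Objectives, hypothesis paragraph: "diagnostic safety (number of melanomas diagnosed". Here safety is a count.
- Design and description of the study: "The main objective is to evaluate the safety of the integration of RCM (diagnostic identification of melanomas", whereas cost-effectiveness is the "comparison of the number of excisions needed to identify 1 melanoma (including the follow-up period". Here safety is identification of melanomas, and the ratio belongs to the economic side.

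The protocol also states aims for delayed diagnosis. Principal Objective: "Experimental design 1 aims at a reduction of over 30% of unnecessary excisions, with less than 2% of melanoma delayed" diagnosis, "and with no tumors thicker than 0.5 mm delayed". The section on expected results repeats the 2% figure. Statistical analysis, directly after the safety outcome, expects under 1% delayed cancer diagnoses in the RCM arm.

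**The concern.** RCM is being tested as a reason to defer excision. The harm to be ruled out is a melanoma that is deferred and found late, or never found. A safety outcome has to respond to that harm.

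Excisions per melanoma is the reciprocal of the positive predictive value among excised lesions. It contains nothing about lesions left in place. A melanoma that is never excised leaves both the numerator and the denominator, and one excised during follow-up re-enters both as though there had been no delay. The count in the Secondary Objectives would fall when melanomas are lost, while the ratio in the Statistical analysis section could improve on the same data. Safety is part of the main objective, so a reader of the results could be shown a favourable safety figure that says nothing about sensitivity.

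**Working it through.** **Inputs.** Control-arm melanoma percentage 7.3%, RCM-arm percentage 14%, 532 subjects and enrolment of 2375 (Statistical analysis); aim of over 30% fewer unnecessary excisions (Principal Objective); 1:1 allocation (Design). Assumptions: control excises every lesion, one lesion per patient, and the same underlying melanoma share in both arms. The miss rates below are illustrative; the protocol gives none.

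**The plan's own figures.** 532 / 0.224 = 2375, as stated. The point here disputes neither number; they only set the base for the counts.

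**The two ratios carry the same information.** With M melanomas and B benign lesions excised, excisions per melanoma = (M + B)/M = 1 + B/M. The NNE is written as malignant over benign. If malignant means melanoma, that is M/B, and excisions per melanoma = 1 + 1/(M/B).

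**Rule.** Let b be the share of benign lesions spared and m the share of melanomas never excised in the RCM arm:

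ratio = [M(1 − m) + B(1 − b)] / [M(1 − m)] = 1 + (B/M) × (1 − b)/(1 − m)

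Control is 1 + B/M. The RCM ratio is no worse exactly when (1 − b) ≤ (1 − m), that is, when m ≤ b. The rule does not depend on the melanoma prevalence.

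**Numbers per 100 lesions.** M = 7.3, B = 92.7. Control: 100/7.3 = 13.7.

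| b | m | Benign excised | Melanomas excised | Excisions per melanoma |
|---|---|---|---|---|
| 30% | 0% | 64.89 | 7.30 | 9.9 |
| 30% | 10% | 64.89 | 6.57 | 10.9 |
| 30% | 20% | 64.89 | 5.84 | 12.1 |
| 30% | 30% | 64.89 | 5.11 | 13.7 |
| 30% | 40% | 64.89 | 4.38 | 15.8 |
| 50% | 30% | 46.35 | 5.11 | 10.1 |

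Break-even at the 30% aim is therefore 30% of melanomas missed. Beyond that the ratio is worse than control.

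**Delay.** Suppose b = 30% and 20% of melanomas are deferred but excised during follow-up, with no further benign excisions. The ratio is (64.89 + 5.84 + 1.46)/(5.84 + 1.46) = 72.19/7.30 = 9.9, identical to the row with nothing missed.

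**Counts per arm at break-even.**
- 7.3% applied to the 532: 266 × 0.073 = 19.4 melanomas, and 30% of these is 5.8, about 6 of 19.
- 7.3% applied to all 2375: 1187.5 × 0.073 = 86.7 melanomas, and 30% of these is 26.0, about 26 of 87.

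**The planned 14% does not settle it.** Read per excised lesion, 14% is 1/0.14 = 7.1 excisions per melanoma. With no melanoma missed, that needs 7.3 × 0.86/0.14 = 44.8 benign excisions, so 52% spared. With 30% missed, it needs 5.11 × 0.86/0.14 = 31.4, so 66% spared. The same figure fits both situations.

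**The case against.** The strongest reply is that this is a labelling slip in a protocol that otherwise attends to missed melanomas. Delayed-diagnosis aims appear in three places, deferred lesions are followed for at least 6 months, safety is given elsewhere as melanomas identified, and diagnosis frequencies are to be compared by chi-square. A miss rate of 10% to 30% would breach the stated aims if the misses surfaced. The illustration also assumes that control excises everything, whereas the control pathway allows digital follow-up, although the Design section expects immediate biopsy to be likely.

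Much of this stands, and it rules out three stronger readings that a reader might infer.

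- *The ratio favours deferral however many melanomas are lost.* It does not. Above m = b it worsens (15.8 against 13.7 at 40% missed with 30% spared).
- *The ratio is the protocol's only safety criterion, so an unsafe arm would pass as safe.* The delayed-diagnosis aims and the count-based definition stand beside it. The arm would look acceptable only on the outcome that the Statistical analysis section names safety.
- *About 26 melanomas per arm are at stake.* That is one reading of the base; the other gives about 6.

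The reply does not remove the defect. The delay figures are worded as aims or estimates, differ (under 1% of cancers, under 2% of melanomas), and are not linked to the outcome called safety. The chi-square would reflect lost melanomas if taken per randomised patient, but not if taken per excised lesion, and the protocol does not fix the denominator. If control also defers lesions, the rule still holds, with the shares of melanomas and benign lesions excised taken relative to control.

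**Conclusion.** The point holds in a bounded form. The Statistical analysis section names an efficiency ratio as the measure of diagnostic safety, in conflict with its own later wording, the Design section and the Secondary Objectives. That ratio is no worse than control whenever the share of melanomas missed is at most the share of benign lesions spared, and it cannot show delay in melanomas excised during follow-up. At the 30% aim, up to 30% of melanomas could be missed with the ratio at or below 13.7. This size rests on control excising all lesions and on 7.3% melanoma; the break-even share itself does not depend on 7.3%. The documents do not show that melanomas will be missed at such rates, nor that the trial as a whole would overlook them. They show that the outcome labelled safety would not reliably reveal it.

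**What to change.** - In the Statistical analysis section, relabel excisions per melanoma as the efficiency outcome and state that neither it nor the NNE is evidence of safety.
- Define safety in both arms by two measures: (a) total melanomas diagnosed by the end of follow-up per randomised patient; (b) melanomas not excised at the first decision but found by the end of follow-up, per randomised patient and as a share of all melanomas found. Report each with the between-arm difference and 95% confidence interval. Measure (a) is needed because (b) cannot see melanomas that are never found; randomisation lets a shortfall in (a) reflect them.
- Align the hypothesis paragraph in the Secondary Objectives and the main objective in the Design section with these definitions.
- Reconcile the under-1% and under-2% delayed-diagnosis figures, which also differ in referring to cancers and to melanomas, and link the result to measure (b).

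The cost is wording only. The Data collection section already records the first decision, the later decision and histology per lesion. No clinical rule changes.

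The downside is imprecision, which should be stated. Two-sided power at 0.05 to detect a 20% relative loss on measure (a) (7.3% against 5.84%) is about 30% with 1187 per arm and 10% with 266 per arm. For measure (b), zero delayed among 86 melanomas gives a one-sided 95% upper limit of 1 − 0.05^(1/86) = 3.4%. Excluding 2% would need ln 0.05 / ln 0.98 = 148.3, so 149 melanomas with none delayed.

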b) "Clinical and dermoscopic evaluation only": following routine therapeutic care (clinical-dermoscopic examinations) clinicians of patients with suspicious lesions (at least one major or minor clinical and / or dermoscopic criterion for malignancy, as per inclusion / exclusion criteria), will make a clinical decision (removal or digital dermoscopic follow-up) without RCM evaluation.

Each participating center will be responsible for its own case history and clinical decisions. Each center will take care of the collection and storage of data. At interim analysis (18 months) collected data and preliminary results will be evaluated collectively and discussed. The investigators at the participating centers have high-level therapeutic-diagnostic pathways in place, as documented by the numerous publications produced by these centers, however, in case of significant discrepancies among the interim clinical performance data, or if requested by individual investigators, some cases may be evaluated independently by other investigators in order to verify diagnostic agreement. These cases may derive either from direct indications from the investigators or randomly selected from the collected cases.

Images will be anonymized and only essential clinical data (sex / age, any significant present or past pathologies) will be provided to the other evaluators.

The definition of the head / neck lesion subset is as follows:

1. Malignant macules with histological diagnosis of melanoma;
2. Benign macules with histological diagnosis of actinic keratoses, solar lentigos, lichen planus-like keratosis, seborrheic keratoses, freckles and junctional / compound / dermal nevi;
3. Benign macules not subjected to biopsy and with clear and defined parameters of clinical, dermoscopic and confocal microscopy benignity;

The main outcome will be the rate of malignant lesions identified within the "RCM evaluation + clinical and dermoscopy evaluation" compared to "Clinical and dermoscopic evaluation only" study arms.

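### The chi-square comparison of diagnosis frequency ignores centre; it is valid, but a centre-stratified analysis would be slightly more precise at no cost (minor)

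*Protocol*

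**What the plan says.** **Test.** Protocol, Statistical analysis: "The differences in the frequency of diagnoses obtained in the two study groups will be calculated and compared using the X2 test (chi-square". This is a two-group comparison. Pooling of the centres is not stated in words; it follows from the test named.

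**Centres and enrolment.** Protocol, Design and description of the study: "This is a prospective randomized 2-arm study (performed in 3 hospitals", and "Randomization will be allocated at a 1:1 ratio". Statistical analysis adds "In the Coordinating Center, an estimated 800 patients will be enrolled (a total of 400 cases per study arm", and for all centres "Each collaborating center will enroll about 800 subjects". A split by arm within a centre is therefore written for the coordinating centre only.

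**Randomisation.** The Stata function "will be used weekly to predetermine the allocation of the subjects, in an alternating random manner, into the two study arms". Stratification by centre is neither stated nor excluded.

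**Centre differences.** Design and description of the study: "Each participating center will be responsible for its own case history and clinical decisions". Independent review of selected cases is foreseen "in case of significant discrepancies among the interim clinical performance data". That is a check on diagnostic agreement, not an adjusted comparison of the arms.

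**Centre in the data.** Under Data collection, the patient code begins with two letters for the city of enrolment.

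**The concern.** Centre is a likely source of variation in this trial. Three hospitals each recruit about a third of the patients and decide locally what to excise and what to follow, and the protocol itself allows for discrepancies between them. If the proportion of patients with a melanoma diagnosis differs by centre, a two-group chi-square treats the between-centre variation as random error. Its standard error is then somewhat too large. The test also cannot correct for an arm that happens to receive more patients from a high-rate centre. A stratified analysis deals with both, using a variable that is already recorded.

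What is at stake is a little precision and some protection against chance imbalance. The validity of the comparison is not at stake.

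**Working it through.** **1. The plan's own figures.** Inputs from Statistical analysis: 7.3% against 14%, 80% power, alpha 0.05, total 532, and 22.4% for the enrolment step.

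Per arm, n = [z(alpha)·√(2·p̄·q̄) + z(beta)·√(p1·q1 + p2·q2)]² / (p2 − p1)², with p̄ = 0.1065, 2·p̄·q̄ = 0.1903, p1·q1 + p2·q2 = 0.1881 and p2 − p1 = 0.067.
- One-sided 0.05: (1.645·0.4363 + 0.8416·0.4337)² / 0.004489 = 261.1, so 262 per arm and 524 in total, within 3% of 532.
- Two-sided 0.05: (1.960·0.4363 + 0.8416·0.4337)² / 0.004489 = 331.6, so 332 per arm and 664 in total.
- Enrolment: 532 / 0.224 = 2375, as stated. Three centres of about 800 give about 2400.

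So 532 is close to a one-sided calculation. The power figures below are for two-sided tests at 5%, which is why they lie near 70% at about 532 patients (266 per arm gives 70.8%). That is a separate matter; here only the difference between the two tests counts.

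**2. Assumptions.** Centre rates are not in the protocol. Assumed: three equal centres, control rates averaging 7.3%, and a common odds ratio of (0.14/0.86)/(0.073/0.927) = 2.067.

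**3. Precision by formula.** With equal arms in each centre, the pooled variance of the risk difference is proportional to P, the sum over arms of p̄(1 − p̄). The stratified variance is proportional to W, which is P minus the between-centre variance of the rates in each arm.

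| Control rates by centre | RCM-arm rates by centre | P | W | √(P/W) |
|---|---|---|---|---|
| 7.3 / 7.3 / 7.3% | 14.0 / 14.0 / 14.0% | 0.1881 | 0.1881 | 1.000 |
| 5.0 / 7.3 / 9.6% | 9.8 / 14.0 / 18.0% | 0.1876 | 0.1861 | 1.004 |
| 3.0 / 7.3 / 11.6% | 6.0 / 14.0 / 21.3% | 0.1865 | 0.1813 | 1.014 |
| 2.0 / 6.0 / 13.9% | 4.1 / 11.7 / 25.0% | 0.1850 | 0.1750 | 1.028 |

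For example, in the third row W = 0.1865 − 0.0012 − 0.0039, to rounding. The pooled standard error is 0 to 2.8% too large. Simulated standard errors agree: the stratified one is smaller by 2.8% (400 per arm per centre) to 3.1% (89 per arm per centre) in the last scenario. At 89 per arm, about 0.4% of this appears even with equal centre rates and reflects small strata, not a real gain.

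**4. Power by simulation** (40,000 runs per setting, equal arms within centre), pooled chi-square against Cochran-Mantel-Haenszel:

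| Control rates | 534 patients | 2400 patients |
|---|---|---|
| equal | 72.0% vs 72.0% | both at least 99.9% |
| 5.0 / 7.3 / 9.6% | 70.9% vs 71.2% | both at least 99.9% |
| 3.0 / 7.3 / 11.6% | 69.3% vs 70.3% | both at least 99.9% |
| 2.0 / 6.0 / 13.9% | 67.0% vs 68.8% | both at least 99.9% |

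**5. Validity.** In these runs the type I error of the pooled chi-square was 4.6 to 5.1%, and the bias of the pooled risk difference was zero within simulation error. With simple randomisation not stratified by centre (20,000 runs per setting, two widest spreads), type I error was 5.0 to 5.1% and the mean risk difference again matched the true one (6.49 against 6.48 points with 177 patients per centre and rates of 3.0 / 7.3 / 11.6%).

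**6. Chance imbalance.** Illustration with no true effect and assumed centre rates of 5/10/15%: if one arm has 440/400/360 patients and the other 360/400/440, the pooled rates are 116/1200 = 9.67% and 124/1200 = 10.33%, a difference of 0.7 points due to centre alone. A stratified estimate removes it. Such a split is unusual: under simple randomisation of 800 patients the standard deviation of one arm's count is √(800·0.25) = 14.1, so a deviation of 40 is 2.8 standard deviations.

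**The case against.** The strongest objection is that nothing here is invalid. Randomisation makes arm independent of centre, the chi-square keeps its size, and its error rate already covers chance imbalance. At the planned enrolment both tests are almost certain to detect 7.3% against 14%. Centre adjustment is also commonly left to a statistical analysis plan, which may exist but is not at hand, and naming a chi-square does not rule out a stratified version. All of this stands, and it is why the point is minor. What remains is that the protocol does name a test, the test has no centre term, and a better-matched one needs no new data.

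A reader might infer stronger versions, which the protocol does not support:
- **That pooling biases the estimate by centre.** Under 1:1 randomisation it does not. If an odds ratio is reported, the pooled value (2.00 to 2.06 in these scenarios) lies slightly below the within-centre 2.07, but that is non-collapsibility, not confounding.
- **That randomisation is stratified by centre, so the analysis must follow.** Stratification is never stated; 400 per arm is given for the coordinating centre only.
- **That weekly replacement of refusals (Data collection) unbalances the arms by centre.** The text describes it as a way to bring both groups to planned size and does not say it has that effect.
- **That precision losses are large because excision rates vary widely.** Assumed excision rates of 30/50/80% or 50/70/90% would widen intervals by about 10% or 7%, but those rates are invented, and the quoted sentence assigns the chi-square to diagnoses, not to excisions.

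**Conclusion.** The point holds as a minor one. The named comparison of diagnosis frequency leaves out centre in a three-hospital trial where local decisions may differ. The analysis is valid and unbiased as written. The cost of ignoring centre is a standard error about 0 to 3% larger and 0 to 2 power points at about 532 patients, with almost no power difference at about 2400. The upper ends need a sevenfold spread in centre rates. The pooled comparison also leaves any chance imbalance by centre in the observed difference. These sizes rest on assumed centre rates, equal centre sizes and a common odds ratio. No conclusion of the trial would become unsafe if the sentence stayed as it is.

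**What to change.** In Statistical analysis, replace the chi-square comparison of diagnosis frequency with a Cochran-Mantel-Haenszel test stratified by enrolling centre, or with logistic regression including centre as a covariate. Report the centre-stratified risk difference with its 95% CI. If a statistical analysis plan already specifies this, align the protocol sentence with it.

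The cost is one sentence. Centre can be read from the existing patient code, no further data or patients are needed, and the stratified test lost no power in any scenario examined.

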**Exclusion criteria:**

- 1) Patients <18 years old
- 2) Comorbid dermatological pathologies that can alter the visualization of the lesions in RCM, such as extensive hyperkeratotic skin diseases or widespread eczema.
- 3) Physiological, general pathological or psychiatric conditions that prevent the patient from being able to lie down for at least 10 minutes (time of RCM evaluation)
- 4) lesions with alterations (ulceration, crust, hyperkeratosis) which prevent RCM visualization.

Additionally, in a smaller population of patients classified at high risk of melanoma, will be evaluated with a total body examination with the RCM (VivaScope 3000) for each melanocytic skin lesion in addition to classic videomicroscopy. Suspected lesions in dermoscopy and / or RCM will be excised. Subsequently, the accuracy of excisions will be compared for both groups, and the benefit of the combined approach to the patient will be calculated. A population of about 300 patients at high risk of developing melanoma (> 100 nevi, > 4 atypical nevi) will be required. These tests will be performed in two of the collaborating outpatient clinics, performed by 2 interchangeable expert specialists (both will examine 50% of the population with dermoscopy and 50% with RCM). Coincident and

discordant data in case of equivocal injury will be compared. Any lesion showing features in dermoscopy and / or confocal that are suspicious of melanoma will be excised. In high-risk patients, any lesions that do not show clear benign features will be routinely monitored with digital videodermoscopy for at least six-months.

The main objective in this case is the quantification of detection of suspected and confirmed malignant lesions on histological examination after excision, with respect to the standard of care (clinical examination + videomicroscopy). The time required for the total-body examination will be measured and compared with a standard videomicroscopy to estimate the cost-benefit value of the procedure.

The previously described statistical tests (chi-square and Z-test) will be applied.

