### **Data collection**

Patients will be coded on the basis of a code generated for each patient enrolled which includes 2 letters (indicating city of enrollment) and 4 consecutive digits (in order of enrolment). In case of multiple lesions for a single patient, lesions will be assigned a letter (A, B, C etc). Essential clinical information for each patient will be collected on an EXCEL file (Gender, age, phototype, number of nevi, number of atypical nevi, family and / or personal history of melanoma, clinical signs of photodamage). For each lesion, the outcome decided during the visit (excision, follow-up) will be indicated. In the event of a lesion referred for follow-up, the subsequent Clinicians' decision (no further follow-up, further follow-up or excision) will be noted.

In the case of excision, upon histological referral, a coded diagnosis will be entered for all the major diagnostic categories. A different EXCEL file, stored on a separate hard-disk and not connected to an external internet network, will collect the code assigned to the patient, the patient's personal data, the date of the visit, any date on which the follow-up is planned / scheduled and personal contact information (telephone / email, etc.) useful for contacting the patient in case the patient does not present for the scheduled follow-up visit. The images coded as described above, without being able to recognize the patient, will be collected on a local Server, with exclusive access allowed by the investigators, through a personal password.

Image management: the images obtained will be coded on the basis of the code generated for each patient enrolled. The images will be stored on local systems (at each individual collaborating center).

Missing data management: any eventual loss of participation by patients' refusal to participate in the study and generated by the randomization process will be compensated the following week, to assure that the number of the patients within both study groups meet the planned dimensions. In case of patients' refusal for surgical intervention, the subject will remain in the study and be monitored over time with a digital follow-up (routine

clinical practice in the case of patients who refuse intervention for lesions without significant suspicion of malignancy), in order to identify lesion modifications, such as increased suspicion of malignancy, enabling a strong recommendation for lesion excision.

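### The between-arm analysis uses none of the baseline predictors already collected; prespecified adjustment would be a small, nearly free gain in precision, not a correction of bias

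*Protocol*

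**What the plan says.** Two between-arm tests are fixed in the protocol's Statistical analysis section. The frequency of diagnoses is "compared using the X2 test (chi-square"). For excisions, "Kolmogorov-Smirnov two-sample Z-test will be used to compare the differences in NNE obtained in the 2 arms". No covariate is named for either. The text after the Exclusion criteria applies the same tests to the high-risk sub-study.

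Data collection lists what is recorded on each patient: "Gender, age, phototype, number of nevi, number of atypical nevi, family and / or personal history of melanoma", plus signs of photodamage. Multiple lesions in one patient are given letters. The section does not say whether these items are recorded before allocation.

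The only sign that the protocol regards any of these variables as prognostic is its definition of the sub-study population, patients "at high risk of developing melanoma (> 100 nevi, > 4 atypical nevi"). No effect size, AUC or R² is given. The randomisation paragraph names no stratification factor.

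**The concern.** When baseline variables predict the outcome, an analysis that ignores them carries more variance than it needs to. Chance differences between arms in age or nevus burden stay in the estimate and widen its interval. The data are already being gathered, so the extra precision would cost almost nothing.

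The protocol's headline aims are a cut of more than 30% in unnecessary excisions and a comparison of melanoma detection, and both feed the cost model. Tighter estimates would help there even where a significance test is not in doubt. The question is how much is being given up.

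**Working it through.** **Inputs from the protocol.** Melanoma 7.3% (control) and 14% (RCM); α = 0.05, sidedness not stated; power 80%; 1:1 allocation; stated N = 532; enrolment target 2375; 400 per arm at the coordinating centre.

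**Input assumed.** Prognostic strength of the covariates: AUC 0.60, 0.70 or 0.80.

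**1. The stated sample size.** With d = 0.067 and mean rate 0.1065,

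n per arm = [z_α √(2 × 0.1065 × 0.8935) + z_β √(0.073 × 0.927 + 0.14 × 0.86)]² / d²

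The two roots are 0.4363 and 0.4337.
- One-sided: (1.645 × 0.4363 + 0.842 × 0.4337)² / 0.004489 gives 262 per arm, 524 in total. This is the closest match to 532 (1.5% below).
- Two-sided: with 1.960 in place of 1.645, 332 per arm, 664 in total.

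The enrolment target is 532 / 0.224 = 2375. It is therefore unclear whether about 532 or 2375 patients enter the comparison, and both are examined.

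**2. Unadjusted two-sided power.** 0.708 at 266 per arm, 0.868 at 400 per arm, and above 0.999 at about 1187 per arm.

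**3. What adjustment could add for melanoma.** At these event rates an AUC of 0.60 corresponds to R² of about 1–2%, 0.70 to about 4–6%, and 0.80 to about 11–15%. Effective n is n/(1 − R²). For example, with R² = 0.05, 266 becomes 266/0.95 = 280 and power rises from 0.708 to 0.730. The two-sided total falls from 664 to 632.

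Simulation (1500 trials per setting; risk difference standardised from a logistic model, against the chi-square):

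| Per arm | Assumed AUC | Power, chi-square | Power, adjusted | Variance ratio (adjusted/unadjusted) |
|---|---|---|---|---|
| 266 | 0.60 | 0.703 | 0.706 | 0.99 |
| 266 | 0.70 | 0.713 | 0.738 | 0.95 |
| 266 | 0.80 | 0.722 | 0.767 | 0.92 |
| 400 | 0.60 | 0.873 | 0.878 | 0.98 |
| 400 | 0.70 | 0.883 | 0.893 | 0.96 |
| 400 | 0.80 | 0.875 | 0.912 | 0.88 |

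The variance saving is about 1 to 8% at 266 per arm and 2 to 12% at 400 per arm. The top end is the least certain, since the R² figures there are 11–15%. Under the null (AUC 0.70, 266 per arm) the rejection rates were 0.049 unadjusted and 0.055 adjusted. The Monte Carlo standard error is √(0.05 × 0.95/1500) = 0.0056, so both are compatible with 5%.

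**4. The same gain as interval width.** The unadjusted 95% half-width is 1.96 × √(0.1881/n), where 0.1881 = 0.0677 + 0.1204. That is 5.2 percentage points at 266 per arm and 2.5 at 1187. An 8% variance cut multiplies each by √0.92 = 0.959, giving 5.0 and 2.4.

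**5. Events available.** At 532 patients, 266 × 0.073 + 266 × 0.14 = 19.4 + 37.2, or about 57 melanomas.

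**6. Excisions.** The protocol plans no direct comparison of excision counts, so no loss relative to a planned analysis can be computed. For scale only: simulated trials of 2375 with assumed covariate effects gave an unadjusted difference in the count of unnecessary excisions 23% more variable than the adjusted one, and 7% when those effects were halved. The result is driven by the assumption.

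**The case against.** The strongest reply is that nothing here is wrong. A chi-square between randomised arms keeps its error rate, chance imbalance is already allowed for in that rate, and covariate adjustment is often left to an SAP, which is not shown. The validity part stands in full. The SAP part stands only in part: the protocol names its tests rather than deferring them, so the choice can be commented on, but an SAP may already add adjustment.

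Some stronger readings are tempting and are not supported:
- **That the collected variables are strong predictors.** No figure says so. Patients are already selected for a suspicious lesion (Inclusion criteria), which may leave less for age and nevus counts to explain.
- **That the chi-square loses precision on unnecessary excisions.** It covers diagnoses. Excisions enter through NNE and the Kolmogorov-Smirnov test, and whether that test suits a ratio of this kind is a separate question. The design section also expects most control patients to need immediate biopsy, so variation in having any excision may be limited in that arm.
- **That adjustment has no downside.** With about 57 events a long covariate list would be thin. The number of suspicious lesions is not a listed field with a stated time of recording; if lesions are lettered after arm-specific evaluation, adjusting for their number conditions on something that follows allocation.

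For scale, the unstated sidedness matters more to sample size: moving from one-sided to two-sided adds 664 − 524 = 140 patients, while R² = 0.05 saves 664 − 632 = 32.

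**Conclusion.** The point holds as an efficiency suggestion of low priority. The protocol fixes unadjusted comparisons while collecting plausible predictors, so some precision is left unused. Under the assumed AUC range the variance saving for melanoma is small, and its power benefit matters only if the analysed set is near 532. At 2375 the remaining benefit is a slightly narrower interval. For excisions the gain could be larger, but its size cannot be established from the protocol. There the more certain benefit is an effect estimate with an interval, which the Kolmogorov-Smirnov test does not supply. All sizes rest on assumed prognostic strength.

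**What to change.** In the protocol or SAP, prespecify a short covariate set recorded before randomisation: age, number of nevi, number of atypical nevi, and personal or family history of melanoma. State when these are recorded.

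- **Melanoma:** logistic regression on arm and these covariates, reported as a standardised risk difference with 95% CI.
- **Unnecessary excisions:** a count per patient, by Poisson regression with robust standard errors, reported as an adjusted rate difference or ratio with 95% CI.
- **Number of suspicious lesions:** include it only if it is recorded before allocation.
- **Chi-square:** keep it as a sensitivity analysis.

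The sample size should not be reduced in anticipation of the gain. The cost is wording and a slightly more complex model, with no new data beyond confirming the time of recording. If only about 532 patients are analysed, the list must stay this short: arm plus four covariate terms is five parameters, or 57/5, about 11 melanomas per parameter.
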